## Abstract

**Background:**

Despite the reduction in glycemic derangement in patients with type 1 diabetes mellitus (T1D) through dietary and therapeutic adjustments implemented before, during and after continuous exercise, evidence for its effectiveness with intermittent forms of exercise, such as soccer, is still lacking.

**Methods/design:**

We designed a study protocol for a randomized, crossover, double-blinded, controlled trial, for the evaluation of the effect that a strategy of dietary and therapeutic modifications may have on safety and performance of persons with T1D in soccer training sessions and cognitive testing. Inclusion criteria comprise: age older than 18 years, more than 2 years since T1D diagnosis, low C-peptide level, a stable insulin regimen, HbA1c less than 9.0% and regular participation in soccer activities. Our primary outcome evaluates safety regarding hypoglycemia events in patients using dietary and therapeutic adjustments, compared with the performance under the implementation of current American Diabetes Association (ADA) usual recommendations for nutritional and pharmacological adjustments for exercise. Additionally, we will evaluate as secondary outcomes: soccer performance, indexed by performance in well-established soccer skill tests, cognitive functions (indexed by Stroop, digital vigilance test (DVT), Corsi block-tapping task (CBP), and rapid visual information processing (RVIP) tests), and glycemic control measured with a continuous glucose monitor (CGM).

**Discussion:**

Dietary and insulin adjustments standardized under a 4-step method strategy have never been tested in a clinical trial setting with intermittent forms of exercise, such as soccer. We hypothesize that through this strategy we will observe better performance by persons with T1D in soccer and cognitive evaluations, and more stable control of glycemic parameters before, during and after exercise execution, indexed by CGM measurements.

**Trial registration:**

ISRCTN, ISRCTN17447843. Registered on 5 January 2017.

**Electronic supplementary material:**

The online version of this article (doi:10.1186/s13063-017-2078-1) contains supplementary material, which is available to authorized users.

## Background

The importance of encouraging people with type 1 diabetes mellitus (T1D) to be physically active is well-established when pursuing goals such as overcoming a sedentary lifestyle, improving weight control, ameliorating pre-existing cardiovascular disease, and improving quality of life [1]. The American Diabetes Association (ADA) recommends that individuals diagnosed with T1D participate in regular exercise in attempts to improve different health outcomes such as weight loss and optimal glycemic control. However, routine practice of this intervention is significantly hampered by the risk of exercise-induced hypoglycemia [2]. Additionally, it is frequently observed that people with T1D, concerned about having hypoglycemic events while exercising, tend to increase their caloric intake excessively, eventually leading to vexing glucose variability and further challenging the execution of physical activity [3].

Prior evidence has focused on the effects of certain therapeutic and dietary adjustments on patients’ performance when they participate in sports that involve continuous physical exercise [4]. However, recent publications demonstrate safety, evidenced by protection in terms of rates of hypoglycemic events by reducing degludec insulin dosage in subjects with T1D, even with different exercise intensity and modality (indexed by lactate threshold and potentiometers) [5].

Therefore, it is pertinent to study similar pharmacological and dietary interventions but with intermittent exercise. This exercise modality is more demanding on the body than continuous physical activity of the same average intensity [6], with a greater rise in body temperature (0.3 °C) and an added elevated blood lactate concentration when compared at a given percentage of VO_2_ max [7]. Concomitantly, sweat loss during intermittent exercise can exceed sweat loss during continuous exercise [8], thereby increasing the reliance on carbohydrate (CHO) as a substrate during this type of physical activity [9].

In contrast to continuous exercise that only comprises the workload intensity and the total duration, intermittent exercise consists of five main components: peak work load intensity, peak workload duration, recovery load, recovery duration, and the mean load [4]. A clinical trial comparing continuous with intermittent physical activity in subjects with T1D showed that a lower amount of exogenous carbohydrate is required to maintain euglycemia during intermittent compared with continuous activity, and this finding was not related to increased hepatic glucose output but to significantly lower glucose disposal in intermittent compared with continuous activity. Metabolically, this was paralleled by increased levels of counter-regulatory hormones (mainly growth hormone and catecholamines), and substantially higher levels of lactate in intermittent activity [10].

A realistic recommendation is that exercisers with diabetes mellitus should take in adequate carbohydrate, along with sufficient (albeit likely reduced) insulin before, during, and after prolonged moderate-intensity or high-intensity workouts to maintain and restore muscle and liver glycogen and blood glucose, especially during that window of opportunity for glycogen repletion right after the end of exercise (within 30 min to 2 h after) [11].

It is also important to note that the speed with which insulin is absorbed and its onset of action may be increased by both local heating and massage at or near the application site. In addition to changes in insulin dosage and CHO intake, exercise itself may be used to prevent hypoglycemia. For instance, performing a brief (10 s) maximal intensity sprint either before or after a moderate intensity exercise session may protect against hypoglycemia onset, at least in the short run [11].

The effect that the modifications on blood glucose levels before, during, and after exercise have on the performance of athletes in this type of sport has not been accurately established, and evidence addressing this hypothesis is scarce [1]. To our knowledge there is only one study [8] in adolescents with T1D that found that hypoglycemia, but not hyperglycemia, impaired both the patients’ sports performance (tennis, basketball, or soccer skills) and their cognitive function. However, this trial had some important limitations including the fact that the sport performance tests were of a relatively short duration and did not demonstrate how blood glucose levels affected mental and physical stamina [12].

Campbell et al. [2] developed a 4-step method that succeeded in protecting participants with T1D from both hypoglycemia and hyperglycemia throughout exercise periods and the 24-h interval following exercise sessions [2]. This method includes the following interventions: (1) 75% reduction of pre-exercise rapid-acting insulin dose (or 50% if intermittent exercise) given before a meal containing 1 g carbohydrate · kg^-1^ 60 min prior to physical activity [13]; (2) post-exercise meal containing 1 g low-glycemic index (GI) carbohydrate · kg^-1^ 60 min after physical activity with 50% reduction on rapid-acting insulin dose [14]; (3) consumption of a bedtime snack containing 0.3 g carbohydrate · kg^-1^ also with a low GI and omitting prandial insulin administration for this meal [15]; and (4) 20% reduction of basal insulin across the day when physical activity is performed [2].

In clinical trials, this 4-step method has demonstrated that it is possible to optimize blood glucose level during and after exercise by making mealtime adjustments to both rapid-acting and basal insulin, and to pre-exercise and post-exercise carbohydrate composition [2]. However, previous clinical trials have focused on evaluating patients’ performance in continuous forms of sports like running or cycling, whereas evidence supporting this 4-step strategy in intermittent activities such as soccer, tennis, and basketball, is still lacking.

Therefore, we designed a protocol for a randomized, crossover, double-blinded, controlled trial to evaluate the effect that this 4-step strategy for blood glucose control will have on patients’ performance in a series of soccer training sessions and cognitive assessments, compared with usual care recommendations. Moreover, in this study protocol, we introduce the evaluation of this 4-step method in a more realistic “real world” scenario of sports practice, with simulation exercises based on the soccer gameplay field. We hypothesize that participants using the 4-step method will yield a better performance both in soccer-simulated sessions and in cognitive function evaluations when compared to the implementation of the usual ADA recommendations. We also expect fewer glycemic derangements and better glycemic control before, during, and after the performance of physical activities, when applying the 4-step method on the participants.

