#### Active intervention: real 4-step method

Participants will come to the laboratory at 7:00 a.m. and we will first obtain a resting, fasted venous blood sample (via venipuncture) for the laboratory evaluations previously listed. The iPro2 Professional continuous glucose monitor (CGM) with Enlite sensor (Medtronic, MN, USA) will be installed at that time. Participants will then consume a standardized cereal-based breakfast meal (sugar-coated corn flakes, peaches, and semi-skimmed milk; 1.3 g carbohydrate · kg^-1^ body mass). At 1:00 p.m. participants will consume a standardized pasta-based lunch meal (pasta, tomato-based sauce, cheddar cheese, olive oil; 1.3 g carbohydrate · kg^-1^ body mass). Between the morning and evening visits, participants will record their self-measured glucose control every 2 h.

At 5:00 p.m. participants will arrive for the evening training session. Before starting this session, they will self-administer a 50% reduced pre-meal rapid-acting insulin dose into the abdomen (the injection site will be at the mid-point between the iliac crest and the navel). Immediately after receiving this insulin dose, participants will consume a pre-exercise carbohydrate bolus (sugar-coated corn flakes, peaches and semi-skimmed milk; 1.0 g carbohydrate · kg^-1^ body mass). Following this bolus, participants will remain rested for 60 min, at which point a finger stick sample for glucose testing will be drawn immediately before starting with the training sessions.

At 60 min post-exercise, participants will self-administer a pre-meal rapid-acting insulin dose reduced by 50%, into the abdominal site contralateral to the previously administered pre-exercise rapid-acting insulin injection. After receiving this insulin dose, participants will consume a carbohydrate-based meal (basmati rice, tomato-based sauce, turkey breast, and an isomaltulose orange flavored drink (10% solution); 1.0 g carbohydrate · kg^-1^ body mass) designed to elicit a low GI (GI = 37) response [2].

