Following this meal the participants will be discharged and will continue recording interstitial glucose values with the CGM until the subsequent morning visits. At 180 min following the post-exercise meal (240 min post-exercise), participants will consume a low-GI bedtime snack (low fat yogurt with honey tap; GI = 38), equivalent to 0.4 g carbohydrate · kg^-1^ body mass, and will omit rapid-acting insulin. In order to improve adherence, participants will be contacted before the bedtime snack to ensure compliance, and they will be encouraged to replicate their sleeping patterns as much as possible prior to the training sessions.

The basal insulin dose after exercise will be reduced by 20% of the pre-trial basal dose. Nevertheless, the timing will be maintained throughout as per each participant’s individual regimen. Twenty-four hours afterwards, participants will return to their usual full basal insulin dose.

At 8:00 a.m. on the morning following each training assessment, participants will return to the laboratory. Here we will obtain another fasting blood sample through venipuncture and subsequently provide them with a standardized breakfast meal (sugar-coated corn flakes, peaches, semi skimmed milk; 1.0 g carbohydrate · kg^-1^ body mass). With this meal, they will self-administer their full unchanged rapid-acting insulin dose.

Following the consumption of breakfast, the participants will be discharged from the laboratory and instructed to maintain CGM for an additional 11 h (i.e., 24 h from exercise cessation). Also during this time, they will continue to monitor their diet using a food record diary and weighing their foods. We will provide the participants with a smartphone application for the recording of this information (MyFitnessPal App).

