#### Control intervention: usual recommendations (sham 4-step method)

Recently, ADA published a position statement about physical activity and diabetes [16]. This statement explained how the variable glycemic responses observed in association with physical activity makes it very difficult to provide uniform recommendations for both the management of food intake and the insulin dosing regimen. Nonetheless, several instructions in this document are intended to help prevent hypoglycemia. To prevent low blood glucose level during prolonged (>30 min), predominantly aerobic exercise, additional carbohydrate intake and/or reductions in the insulin dose are typically required [12–16]. In addition to the changes in insulin regimen and carbohydrate intake, a brief (10 s) maximal intensity sprint could be performed before or after the exercise session, as suggested in the ADA guidelines, to prevent exercise-induced hypoglycemia [12]. The position statement also recommends adjusting daily basal insulin dose with reduced prandial bolus insulin and low-GI carbohydrate feeding following evening exercise for those on multiple daily injections [12]. Finally, inclusion of a bedtime snack, overnight glucose checks, or alarms and automatic pump suspension may also be warranted [16].

Patients allocated to the control group, or sham 4-step Method, will receive current usual recommendations as stated by the ADA [16], but following the scheme established with the real 4-step method (see Table 2 for the comparison for both interventions). Prior to exercise, the CGM will be installed at 7:00 a.m., and they will receive their meals in the same amount and frequency as in the real 4-step method, consisting of a breakfast at 8:00 a.m., lunch at 1:00 p.m. and pre-exercise meal at 5:00 p.m. All of the three meals will have the same caloric content as in the real intervention, and there will be no insulin modification for the first two meals. Assuming that they will be performing moderately intense physical activity later in the day, for up to 60 minutes, this group will receive a rapid-acting insulin dose that will be 75% of their usual dose concomitantly with the 5:00 p.m. meal prior to the onset of physical activity.

**Table 2 Tab2:** Scheme comparison of interventions delivered in the real and sham 4-step methods

Time		Real 4-step method	Control (sham) 4-step method
8:00 a.m.	Breakfast	Standardized cereal-based breakfast	Standardized cereal-based breakfast

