**Fig. 5 Fig5:**
[figure not shown]
SPIRIT flow diagram. (A summary of the planned study interventions and assessments)

Stroop testThe Stroop test is a commonly used neuropsychological tool that measures selective attention and mental processing speed among the cognitive functions that could be affected by attentional fatigue [22]. Campbell et al. utilized the Stroop test in a clinical trial that evaluated participants with T1D during physical activity in a sports camp. The investigators found that reading and color recognition ability were susceptible to impairment as a result of hypoglycemia [12].Commercially available Stroop Color and Word Tests (WPS Publish, Alaska, USA) will be used to assess cognitive processing in our participants. Scores will be determined for reading ability, color recognition, and interference; the latter will be used as an index of the subject’s capacity to maintain attention during the interference caused by the color changes in the typed words [23].Stroop testing will take place immediately following each soccer training session and during the morning evaluation at 8:00 a.m. on the next day. Each of these tests will take 2 to 5 min (time limit of 45 s per slide) for the participants to complete. Participants will be asked to complete the test using three slides: (1) read as many colored words as possible in 45 s; (2) name as many colors of a group of “X” letters as possible in 45 seconds; and (3) name the color in which a word is printed (e.g., “blue”, “green”, or “red” ink) and not the word itself, which is a name of a color (e.g., the word “red” printed in blue ink instead of red ink). Naming the color of the word during this “interference” takes longer and is more prone to errors than when the color of the ink matches the word that names the color [16]. Reading, color naming, and interference scores will be converted to *T* scores according to the manual of Golden and Stroop for further analyses.Digit vigilance testThe digit vigilance test (DVT) works as a measure of sustained attention and psychomotor speed. Participants will be asked to cross out a specific target number (6) as quickly as possible, which appears randomly within 59 rows of 35 single digits on two pages. The examiner will observe the subject's performance on the demonstration rows and then on the first five rows of the test to determine whether corrective feedback is required to discourage an inefficient or poorly motivated response style (e.g., going too fast and missing numbers or going too slow and focusing attention on each individual number). Total time and errors of omission will be recorded. For the first (practice) administration, all participants will be asked to complete the standard format (target = 6) [24].Corsi block-tapping taskThe Corsi block-tapping task (CBT) is widely used for the assessment of visual-spatial short-term memory, both in clinical practice and in experimental research settings. Basically, it is a span task and, as such, a visual-spatial analog to the digit span, as an index of verbal short-term memory. The examiner taps a sequence of blocks, which the participant must repeat subsequently in the correct sequential order. By increasing the length of the sequences, the capacity of the visual-spatial short-term memory can be measured [25].The participant will be seated in front of the examiner, who subsequently will tap the cubes starting with a sequence of two blocks. Two trials will be given per block sequence of the same length. If at least one of these is repeated correctly, the next two trials of a sequence of an increased length will be administered. The cubes will be touched with the index finger at a rate of approximately one cube per second (with no pauses between the individual cubes). The participant will have to tap the cube sequences in the same order immediately after the examiner finishes. The sequences will gradually increase in length. The test will be terminated if the participant fails to reproduce two sequences of equal length. Only a completely, correctly repeated sequence will be scored as correct; self-corrections will be permitted.Rapid visual information processing taskThe rapid visual information processing task (RVIP) is a serial detection task used to probe visual sustained attention and working memory processes. The design of the task consists of a stream of single digits (Arabic numerals 1–9) presented at a rate of 100–110 per minute. Participants are required to detect targets comprising a sequence of three consecutive odd or three consecutive even numbers. In a typical paradigm, targets are presented at a rate of four per 30 s. The critical performance variables include the number of correct responses (“hits”), the reaction time for hits, and the number of errors of commission (response in the absence of a target) [26].This RVIP version will be programmed using e-prime (Version 1.1. Psychology Software Tools, Inc., www.pstnet.com). White numbers between 0 and 9 (excluding 1) will appear in the center of a black computer screen. Each number is presented for 600 ms without a time gap between two succeeding numbers. The participant will have to detect three target sequences (“2–4–6”, “3–5–7”, and “4–6–8”) and respond to them (within 1800 ms after the onset of the last number) by pressing the space bar on the keyboard when the last number of a target sequence appears. The three target sequences will be displayed on the screen during the whole session in order to help the participants remember.Each block will be composed of 150 numbers that appear in a pseudo-random and fixed order; four target sequences will be included in 50 numbers. There will be 72 target sequences that appear during the 9-min test session. In order to prevent a sequence effect, six different RVIP versions will be created by varying these six blocks and then balancing them and pseudo-randomly assigning them to the participants. Hits (H), false alarms (FA) and reaction time (RT) will be recorded by the computer. All RTs shorter than or equal to 100 ms will be excluded from further analyses.

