## Discussion

During clinical trials the 4-step method has been demonstrated to optimize blood glucose levels during and after exercise by making mealtime adjustments to both rapid-acting and basal insulin and to pre-exercise and post-exercise carbohydrate composition [2]. The first step of this method protects individuals with T1D from concomitant and early exercise-induced hypoglycemia [6], the second step prevents a rapid rise in blood glucose because of an overcorrection with food using a low-GI carbohydrate meal [7], and the third and fourth steps are intended to guard against late-onset exercise-induced hypoglycemia after physical activity [2, 11].

Intermittent exercise, such as soccer, is more demanding on the body than continuous exercise of the same average intensity [21]. The 4-step method has never been tested in a clinical trial setting for the evaluation of intermittent forms of exercise, such as soccer.

We expect that this protocol will stimulate the development and execution of clinical trials to evaluate dietary and pharmacological interventions that will help patients with T1D engage in physical activity, reduce the risk of glycemic derangements while conducting exercise, and at the same time obtain the best physical and cognitive performance possible.

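### Same-evening soccer and Stroop results cannot support a claim for the whole 4-step method, because steps 2 and 3 come after those tests

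*Protocol article*

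**What the plan says.** The hypothesis in the Background is about the strategy as a whole: "We hypothesize that participants using the 4-step method will yield a better performance both in soccer-simulated sessions and in cognitive function evaluations". The text that introduces the cognitive tests under Secondary outcomes repeats it for soccer and cognition.

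The Active intervention section sets the order of the steps:

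- **Step 1**, at 5:00 p.m. before the session: "they will self-administer a 50% reduced pre-meal rapid-acting insulin dose into the abdomen".
- **Step 2**: "At 60 min post-exercise, participants will self-administer a pre-meal rapid-acting insulin dose reduced by 50" per cent.
- **Step 3**: "At 180 min following the post-exercise meal (240 min post-exercise), participants will consume a low-GI bedtime snack".
- **Step 4**: "The basal insulin dose after exercise will be reduced by 20% of the pre-trial basal dose".

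Table 3 and the Outcomes section give one training session per period (visits 3 and 6, three weeks apart). The section on the shooting test puts all five soccer assessments (LSPT, LSST, LIST-P, LSPT, LSST) in one fixed sequence within that session. For cognition, "Stroop testing will take place immediately following each soccer training session and during the morning evaluation at 8:00 a.m. on the next day". Table 3 lists cognitive evaluations at visits 3 and 6 and again at visits 4 and 7.

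**The concern.** A meal and a snack given after a test has ended cannot change its result. If the soccer scores differ between arms, the hypothesis as worded invites the report that the 4-step method improves performance, although at least two of its steps had not yet been given. If the scores do not differ, the same wording invites the conclusion that the method does not help performance, although those steps never had a chance to act. Participants cross over after their one session, so no later session is played under the same regimen on which the late steps could show an effect.

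Cognition is measured both before and after the late steps. The two rounds therefore answer different questions under one hypothesis.

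**Working it through.** The plan gives no figure on this point. The check is to put the steps and the tests in order.

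**1. What differs between arms before the first soccer test.** Table 2 gives both arms the same breakfast and lunch with unchanged insulin, and the same 1 g/kg carbohydrate at 5:00 p.m. The one difference that applies to every participant is the 5:00 p.m. rapid-acting dose, about 60 min before the session.

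**2. Where each step falls.**

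| Step | Timing in the article | Before the soccer tests and post-session Stroop? | Before 8:00 a.m. next day? |
|---|---|---|---|
| 1 | 5:00 p.m., pre-exercise | Yes | Yes |
| 2 | 60 min after exercise | No | Yes |
| 3 | 240 min after exercise | No | Yes |
| 4 | Inconsistent (see 4) | Not on the post-exercise wording; possible for some on the others | Depends on the participant's basal hour |

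**3. Clock times.** The Active intervention section continues CGM for 11 h after the 8:00 a.m. visit to reach 24 h from the end of exercise. Since 8 + 11 = 19, exercise ends at 7:00 p.m. Step 2 is then at 19 + 1 = 20 (8:00 p.m.) and step 3 at 19 + 4 = 23 (11:00 p.m.). The 8:00 a.m. tests (hour 32) follow step 2 by 32 − 20 = 12 h and step 3 by 32 − 23 = 9 h. Table 2 instead shows the post-exercise meal at 7:00 p.m., which would put the end of exercise at 6:00 p.m. For any end between 6:00 and 8:00 p.m. the gaps are 11 to 13 h and 8 to 10 h. The order does not change. Stroop takes 2 to 5 min directly after the session, so it is finished well before step 2.

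**4. Step 4.** The Background describes the basal reduction as covering the whole exercise day. The Active intervention section applies it to the dose after exercise but keeps each participant's own timing. Table 2 places it at the participant's regular basal hour. The Control intervention section treats it as a post-exercise change. Pump users are eligible under Table 1. A morning basal dose or a pump rate could therefore be reduced before the session on some of these readings and not on others.

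**5. The main pre-test contrast.** The active arm takes 100 − 50 = 50% of the usual dose. For control, the text says "this group will receive a rapid-acting insulin dose that will be 75% of their usual dose", whereas Table 2 shows a 75% reduction, that is 100 − 75 = 25% of usual. Active minus control is 50 − 75 = −25 percentage points of the usual dose on the text and 50 − 25 = +25 points on the table. The direction of the contrast reverses.

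**6. The article's own rationale.** The Discussion credits step 1 with protection during and soon after exercise, and says "the third and fourth steps are intended to guard against late-onset exercise-induced hypoglycemia after physical activity". This agrees with the ordering above.

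**The case against.** The strongest reply is that the trial randomises the order of two complete packages. A difference in soccer scores is a valid consequence of assignment to a package, whichever component produced it, and the Discussion already tells readers which step acts when. The Research aim is safety, with soccer performance exploratory. This stands: the comparison is sound, and the fault lies in what the hypothesis attributes to it.

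Four stronger readings are tempting, and the article does not support them.

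- *The performance objective cannot be answered for the strategy at all.* The hypothesis also covers cognition, and the tests at visits 4 and 7 follow steps 2 and 3.
- *Three of the four steps are absent for every soccer outcome.* Only steps 2 and 3 are certain to come later. Step 4 is unresolved.
- *The whole cognitive battery is given straight after the session.* That timing is stated for Stroop only. The other tests are placed by visit.
- *The two cognitive rounds will be pooled.* Nothing says so, and the Outcomes section refers to two separate rounds. Separate reporting is a safeguard here and does not correct a stated error.

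**Conclusion.** The point holds as an attribution problem for secondary or exploratory outcomes. For LIST-P, LSPT, LSST and same-evening Stroop, two of the four steps (2 and 3) cannot contribute in any participant. What remains is step 1, plus step 4 in those whose basal reduction falls before the session, a number the article does not allow one to estimate. The conclusion assumes that the post-exercise intervals in the text (60 and 240 min) govern over the clock times in Table 2.

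The primary outcome counts hypoglycemia over the 24 h after the session, so it spans the later steps. Neither it nor its sample size is affected. Next-morning cognition can speak for the strategy, with one caveat: on the post-exercise wording, a participant whose basal hour falls after 8:00 a.m. might not yet have had step 4. That is a further reason to settle its timing.

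**What to change.** 1. Restate the soccer hypothesis, and the same-evening cognitive one, as the effect of the pre-session components against control.
2. Name the next-morning cognitive tests (visits 4 and 7) as the cognitive outcome for the full strategy, and report the two cognitive time points separately.
3. Keep strategy-level conclusions for 24-h hypoglycemia, post-session and overnight CGM, and next-morning cognition.
4. Reconcile the statements on step 4 timing in the Background, Active intervention, Table 2 and Control intervention, and record for each participant whether the basal reduction came before the session.
5. Reconcile the control arm's pre-exercise dose between the Control intervention text and Table 2, because the restated hypothesis depends on it.

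Items 1 to 3 change wording and reporting only. Item 4 adds one recorded data item, and item 5 is a correction of the document. No new visits, tests or participants are needed. The price is a narrower performance claim.
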